## Abstract

Core stability is fundamental to posture, balance, and force transmission throughout the kinetic chain. Although traditionally associated with athletic performance, emerging research highlights its broader applicability to recreational fitness. This study investigates the effects of an eight-week core training program on muscle hypertrophy, static balance, and neuromuscular control in recreationally active, non-athletic adults. Participants will undertake a structured intervention comprising progressive triads targeting core stability, strength, and power. Assessment methods include surface electromyography (EMG), ultrasound imaging, three-dimensional force plates, Kinovea motion analysis, and the Satisfaction With Life Scale (SWLS) questionnaire. Expected outcomes include enhanced core muscle activation, improved static balance, and increased core-generated force during overhead medicine ball slam trials. Additionally, the intervention aims to facilitate hypertrophy of the transverse abdominis, internal oblique, and lumbar multifidus muscles, contributing to spinal resilience and motor control. This protocol bridges gaps in core training methodologies and advances their scalability for recreational populations. The proposed model offers a structured, evidence-informed framework for improving core activation, postural stability, muscle adaptation, movement efficiency, and perceived quality of life in recreationally active individuals.

## 1. Introduction

Core stability is a fundamental component of human movement, forming the basis for effective posture, balance, and force transmission throughout the kinetic chain [1]. A wealth of research underscores the pivotal role of the core musculature in mitigating injury risk and enhancing physical performance. These findings highlight the need for targeted interventions aimed at improving strength, endurance, and neuromuscular control [2,3,4].

Beyond athletic benefits, core stability serves as a key public health component, contributing to injury prevention, musculoskeletal resilience, and long-term movement efficiency. By enhancing neuromuscular engagement and postural endurance, structured core training protocols offer accessible solutions for mitigating the rising prevalence of sedentary-related dysfunctions in the general population. The core is widely understood as an integrated system comprising the passive spinal column (bony and connective structures), active musculature, thoracolumbar fascia, and neural control mechanisms [5,6]. The musculature itself includes the back, abdominal, pelvic floor, diaphragm, hip, and gluteal muscles, which collectively stabilize the spine, facilitate functional movement, and transfer forces between the upper and lower extremities [7,8]. Akuthota and Nadler [9] conceptualized the core as a three-dimensional structure, likened to a box with the diaphragm forming the roof, the pelvic floor the base, and the abdominal and dorsal muscles comprising the walls. While traditionally focused on the lumbar spine and pelvis, more recent models, such as Kolar et al.’s [10] Integrated Spinal Stabilization System (ISSS), emphasize a holistic approach by incorporating the cervical spine alongside deep cervical flexors, spinal extensors, and core musculature of the thoracic and lumbar regions. This expanded view reflects the increasingly recognized role of the core in maintaining both static and dynamic stability across the entire spinal column.

Beyond stabilization, the core serves as a critical hub for force transfer, enabling efficient and coordinated limb movements. As McGill [11] explains, the core functions primarily as a stabilizer and force conduit rather than a prime mover. Completing, Malanga et al. [12] describe its dual role as a stabilizer and a force generator during limb initiation. These complementary perspectives underscore the centrality of the core in the human motor chain, as highlighted by Hoogenboom and Kiesel [13].

Despite its importance, scientific debate persists regarding which muscles serve as primary stabilizers and how they should be prioritized during core training. Some models distinguish between “local” and “global” muscles [14,15], while others emphasize the coordinated activation of all trunk muscles as task-dependent [16,17]. Contemporary approaches frequently categorize core muscles into stabilizing muscles and movement-producing muscles, underscoring the critical role of neuromuscular control in dynamic stabilization [18]. Stability, therefore, is less a product of strength alone and more reliant on endurance and motor control patterns, as insufficient endurance or control—rather than strength—may compromise stability in both everyday and athletic activities [19,20].

Integrated core training programs must address this complexity, balancing the demands of strength, endurance, and neuromuscular coordination. This study seeks to explore these elements through a structured intervention program designed to evaluate the effects of core training on muscle hypertrophy, static balance, and functional motor control.

### 1.1. Core Training in Recreational Exercisers

Core training methodologies have progressed significantly, shifting from traditional static exercises to dynamic and functional protocols aimed at optimizing neuromuscular coordination, force transmission, and movement efficiency across diverse populations [4,21,22,23,24,25,26,27,28,29,30,31]. While initial core interventions primarily targeted athletic performance enhancement, recent research emphasizes their applicability for recreational fitness, providing benefits such as postural stabilization, movement precision, and injury prevention [32,33,34].

Rodríguez-Perea et al. [32] demonstrated that core-specific protocols significantly enhance postural stability, throwing velocity, and jump mechanics, reinforcing the utility of structured core training for general fitness practitioners. Similarly, Tallent et al. [33] found that neuromuscular adaptations from core exercises improve intermuscular coordination and corticospinal excitability, supporting their role in movement efficiency and injury resilience in previously inactive individuals. Zemková & Zapletalová [34] further emphasized that core stability training enhances spinal health, back muscle endurance, and functional movement, making it highly relevant for recreational fitness populations.

### 1.2. Transitioning from Athlete-Focused Protocols to Recreational Applications

Despite the extensive research conducted on core training in athletic contexts, its principles can be effectively adapted for non-athlete individuals seeking to enhance spinal stability, movement control, and long-term physical well-being [4,22,23,24,25,26,27,28]. Contrary to the high-intensity, sport-specific programming that is customary for elite athletes, recreational individuals stand to benefit from scalable core training strategies that emphasize gradual progression, postural endurance, and movement efficiency [35]. Such scalable strategies align with public health initiatives, as they offer accessible and adaptable solutions for injury prevention, workplace wellness, and movement rehabilitation, benefiting diverse populations beyond competitive athletes.

Research has demonstrated that dynamic and functional core exercises, which were initially developed for sports applications, can be equally beneficial for general fitness when appropriately scaled and structured. Core training strategies, which include stability-focused drills, progressive strength exercises, and controlled power movements, have been shown to enhance coordination, neuromuscular control, and posture alignment. These strategies can promote injury prevention and movement quality without excessive physical strain. [32,33,34].

Additionally, while athletic protocols prioritize peak power output, recreational fitness adaptations emphasize functional movement training, ensuring long-term accessibility and adherence. The integration of bodyweight exercises, resistance-based stability drills, and progressively loaded core exercises has been demonstrated to enhance core endurance and structural stability. This, in turn, has been shown to reinforce movement efficiency and musculoskeletal resilience [36].

Core training differs from traditional abdominal and back strengthening approaches in both scope and function. While conventional methods often isolate superficial muscles (e.g., rectus abdominis, erector spinae) through repetitive flexion or extension, core training emphasizes integrated, multi-planar control of the trunk and pelvis. This distinction is particularly relevant in sports requiring rotational power, postural endurance, and dynamic stabilization—such as tennis, golf, martial arts, and handball—where core-based strategies have demonstrated superior transfer to performance and injury prevention [37,38].

### 1.3. Core Training as a Foundational Component of General Fitness

Core stability plays a critical role in human movement, contributing to postural alignment, neuromuscular engagement, and effective force transmission throughout the kinetic chain [6,7,8,9,10,11]. Research confirms that structured core training reduces injury susceptibility, enhances dynamic balance, and improves spinal integrity, making it an essential component of recreational fitness programs. These benefits extend far beyond individual fitness, directly supporting public health strategies focused on reducing musculoskeletal disorders, optimizing movement efficiency, and promoting lifelong functional mobility across diverse populations.

Rodríguez-Perea et al. [32] and Tallent et al. [33] emphasize that structured core interventions enhance deep-core muscle activation, thereby reinforcing motor control strategies that mitigate compensatory movement patterns and augment spinal durability. Additionally, Zemková & Zapletalová [34] emphasize that progressive core stability training optimizes postural endurance, ensuring long-term movement efficiency for general fitness practitioners. Furthermore, the core training method has been associated with various neuromuscular adaptations, which, according to recent literature [33,34], may include improved motor unit recruitment, greater intermuscular coordination, and enhancements in corticospinal excitability. It is hypothesized that these mechanisms facilitate more efficient movement execution, thereby potentially underpinning the observed improvements in strength, balance, and postural control following core-specific interventions.

The findings, when considered collectively, support the broad applicability of core training beyond the context of competitive sports, serving as a critical intervention for movement precision, injury prevention, and functional mobility. The implementation of structured, scalable protocols is instrumental in ensuring accessibility for non-athletes, thereby reinforcing neuromuscular coordination, postural resilience, and quality of life improvements across diverse fitness levels.

The objective of this study is to design, implement, and evaluate a structured eight-week core training protocol intended to enhance core muscle activation, postural control, deep-core hypertrophy, movement efficiency, and perceived quality of life in recreationally active adults. The protocol has been developed with the objective of enhancing neuromuscular activation, postural stability, muscle hypertrophy, and functional movement efficiency in healthy, active adults. The protocol under consideration integrates progressive core-specific exercises with the objective of optimizing core muscle engagement. It is hypothesized that this will result in enhanced spinal integrity, improved kinetic chain coordination, and elevated athletic performance metrics. Therefore, the scientific hypothesis of the study is as follows:(1)The eight-week core training program will enhance the activation of the rectus abdominis, the external oblique abdominis, and the iliocostalis lumborum muscles.(2)The eight-week core training program will enhance core-generated force output as measured by the medicine ball slam exercise on a force plate.(3)The eight-week core training program will help improve the static balance of the participants.(4)The eight-week core training program will enhance the muscle thickness of the transverse abdominis, internal oblique abdominis, and lumbar multifidus, as assessed via ultrasound imaging.(5)The eight-week core training program will enhance torso and arm angular velocity during the medicine ball overhead slam, as measured through biomechanical analysis using Kinovea software.

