## 2. Experimental Design

### 2.1. Trial Design

This study has been prospectively registered on ClinicalTrials.gov under the identifier AUTH-CORE-STUDY NCT07025395, ensuring transparency and alignment with international standards for interventional research protocols.

The present study protocol has also been developed and reported in accordance with the SPIRIT 2013 Statement (Standard Protocol Items: Recommendations for Interventional Trials) [39], which provides guidance for the essential content of clinical trial protocols. Furthermore, the protocol adheres to the Template for Intervention Description and Replication (TIDieR) checklist and guide [40] and the Consensus on Exercise Reporting Template (CERT) [41], ensuring comprehensive, transparent, and replicable documentation of the core training intervention.

All completed checklists (SPIRIT, TIDieR, CERT) and the ClinicalTrials.gov registration certificate are available to reviewers and readers in Supplementary File S2. The official approval letter from the Ethics Committee is provided separately in Supplementary File S3.

This study employs a two-parallel group randomized controlled trial (RCT) design. The experimental group will undergo structured core training, while the control group will continue regular physical activity without targeted interventions. Detailed descriptions of exercise parameters, progression models, training environment, and measurement techniques are provided to enhance transparency and reproducibility.

The study protocol has been reviewed and approved by the Local Ethics Research Committee of the School of Physical Education and Sport Science at Serres, Aristotle University of Thessaloniki (Approval Code: ERC-013/2025, issued on 11 March 2025), in accordance with the University’s Code of Ethics for Research Involving Human Participants, the principles of the Declaration of Helsinki [42], and the EU General Data Protection Regulation (GDPR-EU 2016/679). All participants will provide written informed consent prior to their involvement, and personal information will be handled confidentially.

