### 2.5. Sample Size Calculation

To determine the appropriate sample size for this study, a power analysis was conducted using G*Power 3.1 software [43]. The analysis was based on a repeated-measures design with two groups (experimental vs. control) measured at baseline and post-intervention. The following parameters were used: Effect Size (Partial η^2^) = 0.06 (medium effect); Cohen’s d = 0.50. Alpha Level (α) = 0.05 (5% significance threshold); power (1 − β) = 0.80 (80% probability of detecting a real effect); two measurement points (pre- and post-intervention); and two groups (experimental and control). According to the established criteria, the minimum requisite sample size for achieving adequate statistical power was computed to be 34 participants, with 17 participants allocated to each group. The objective of this study is to include and evaluate 40 participants, with 20 subjects in each group, to account for potential participant dropout. This methodological approach ensures that the study can detect meaningful differences in vertical ball strength, muscle activation (EMG), dynamic balance, angular velocity, muscle hypertrophy, and psychological impact (SWLS scores) with sufficient precision.

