### 3.5. Statistical Analysis

All statistical analyses will be conducted using IBM SPSS Statistics (version 29, IBM Corp., Armonk, NY, USA). Normality checks will be performed via the Shapiro–Wilk test (small to medium samples) supplemented by histograms, Q-Q plots, and skewness/kurtosis assessments.

Reliability Analysis:SWLS questionnaire consistency will be assessed using Cronbach’s alpha (>0.70).Item-total correlations will ensure meaningful contributions to overall scoring.

Inferential Testing:Within-group comparisons: paired samples *t*-test (normal data) or Wilcoxon Signed-Rank test (non-parametric).Between-group comparisons: independent samples *t*-test (parametric) or Mann–Whitney U test (non-parametric).Repeated-measures ANOVA will assess pre- and post-intervention changes, applying Bonferroni corrections for multiple comparisons.

Effect Size and Correlations:Cohen’s d for *t*-tests, Partial Eta Squared (η^2^) for ANOVA.Pearson’s correlation (parametric) or Spearman’s rank correlation (non-parametric) to explore variable associations.

Additional Measures:Homogeneity of variance was tested via Levene’s test.Intention-to-treat (ITT) analysis for participant dropout management, using multiple imputation techniques to mitigate bias.

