### 4.6. Comparative Analysis and Study Implications

The structured eight-week core training protocol is expected to yield substantial post-intervention differences between the experimental and control groups, thereby reinforcing the effectiveness of targeted core interventions.

Neuromuscular and Biomechanical Adaptations: The experimental group is anticipated to display greater muscle activation, force output, and core-driven movement efficiency, surpassing baseline measures and outperforming the control group in medicine ball slam performance and EMG activation profiles [24].Balance and Postural Control Enhancements: Quantifiable improvements in static and dynamic balance tests are expected in trained individuals, demonstrating superior lower-limb stabilization and kinetic chain coordination compared to non-core-trained participants [28].Structural and Psychological Benefits: Increased deep-core muscle thickness, spinal endurance, and subjective life satisfaction are projected for trained participants, reinforcing both physical resilience and mental well-being through structured core activation strategies [30,61].

These findings will support the scalability of core training methodologies beyond elite athletic populations, providing valuable applications for recreational fitness, rehabilitation, and preventive health strategies [62,63].

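### The five hypotheses name no comparator, and section 3.5 lists within-arm tests beside between-arm tests without saying which one decides

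*Protocol article*

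**What the plan says.** The hypotheses stand at the end of section 1.3. All five take the form that the programme will raise or improve an outcome. The second is "The eight-week core training program will enhance core-generated force output as measured by the medicine ball slam exercise on a force plate" and the third is "The eight-week core training program will help improve the static balance of the participants". None names the control group or a difference between arms.

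Section 3.5 lists three families of inferential test for all outcomes together:

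- "Within-group comparisons: paired samples *t*-test (normal data) or Wilcoxon Signed-Rank test (non-parametric");
- between-group comparisons by independent-samples t-test or Mann–Whitney U test;
- "Repeated-measures ANOVA will assess pre- and post-intervention changes", with a Bonferroni correction.

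No test is assigned to a hypothesis, the group-by-time interaction is not named, and nothing says which result counts if they disagree.

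The design itself is comparative. Section 2.1 says "This study employs a two-parallel group randomized controlled trial (RCT) design", and section 2.5 says of the power calculation "The analysis was based on a repeated-measures design with two groups (experimental vs. control) measured at baseline and post-intervention". Section 3.4.4 describes the control routine as serving the comparison between groups. Section 4.6 expects the experimental group to do two things at once: "surpassing baseline measures and outperforming the control group in medicine ball slam performance and EMG activation profiles".

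**The concern.** A hypothesis without a comparator can be met, as worded, by a pre-post improvement among the people who trained. The third hypothesis, on static balance, is the plainest case. With a paired test available as an inferential test, the report could call a hypothesis supported because the experimental arm changed, or because it changed significantly and the control arm did not. Neither result tests the effect of the programme. The first also contains everything else that happens over eight weeks. The second compares two p-values instead of estimating the difference between the arms.

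Shared change is plausible here. Section 2.3 requires regular exercise of all participants, and section 3.4.4 has the control arm train its trunk muscles twice a week. Section 5 says that there are no pilot data, so the size of any retest gain on the slam is unknown. Section 3.4.4 says that the control routine was designed to cause no measurable change. A reader who takes that design aim as fact would be the more inclined to credit any change in the experimental arm to the programme.

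**Working it through.** **Does the sample size show which test decides?** Inputs from section 2.5: "Effect Size (Partial η^2^) = 0.06 (medium effect); Cohen’s d = 0.50", alpha 0.05, power 0.80, two groups, two time points. The pre-post correlation rho is not stated; 0.5 is assumed.

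- Effect size: f = √(0.06/0.94) = 0.2526, or the conventional 0.25.
- Noncentrality for a within-subject term: λ = f² × N × m/(1 − rho) = 0.0625 × 34 × 2/0.5 = 8.5, on 1 and 32 degrees of freedom.
- Power is 0.807 (0.815 with f = 0.2526), and N = 34 is the smallest even total that reaches 0.80. The stated figure is reproduced.

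In a design with two groups and two time points, the group-by-time interaction and the time main effect have the same λ and degrees of freedom in this calculation. The figure of 34 fits both, so it cannot show which term was meant. The between-subjects variant gives 98 and was not the one used.

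**Error of each decision rule when the programme has no effect.** Assumptions that the article does not give: both arms gain the same true amount d (in baseline SD), the SD is equal at both times, and rho is 0.5 or 0.8. The 20 per arm is from section 2.5. Tests are two-sided at 0.05.

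1. *Paired test in the experimental arm.* The SD of change is √(2(1 − rho)), which is 1.000 at rho 0.5 and 0.632 at rho 0.8. So d_z = d/√(2(1 − rho)), with noncentrality d_z × √20 on 19 degrees of freedom.
2. *Experimental arm significant, control arm not.* The arms are independent, so the probability is p(1 − p), with p from rule 1.
3. *Between-arm test of change.* The expected difference is d − d = 0, so the test keeps its nominal level.

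| rho | gain d | d_z | rule 1 | rule 2 | rule 3 |
|---|---|---|---|---|---|
| 0.5 | 0.2 | 0.200 | 14% | 12% | 5% |
| 0.5 | 0.3 | 0.300 | 25% | 19% | 5% |
| 0.5 | 0.5 | 0.500 | 56% | 25% | 5% |
| 0.8 | 0.2 | 0.316 | 27% | 20% | 5% |
| 0.8 | 0.3 | 0.474 | 52% | 25% | 5% |
| 0.8 | 0.5 | 0.791 | 92% | 7.5% | 5% |

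Examples for rule 2: 0.136 × 0.864 = 0.118; 0.247 × 0.753 = 0.186; 0.918 × 0.082 = 0.075. Its ceiling is 25%, reached at p = 0.5. It falls again once both arms usually reach significance, so the 92% and the 25% do not belong to the same scenario.

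A simulation of 40,000 trials at rho 0.5 agrees. Rule 1 gave 13.6%, 24.9% and 56.3%; rule 2 gave 11.8%, 18.8% and 24.3%; rule 3 gave 5.0%, 5.0% and 4.9%.

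**The case against.** A reader might infer that the hypotheses are matched to within-group tests, that efficacy will be declared from the experimental arm alone, and that the randomised control is wasted. The documents do not support that. Section 3.5 matches no test to any hypothesis, lists between-group tests next to the paired ones, and gives the paired test no priority by naming it first. Sections 2.1, 2.5, 3.4.4 and 4.6 all point to a comparison with control, and section 4.6 asks for improvement on baseline and superiority to control together. In a randomised trial, saying that a programme will enhance an outcome can also be read as a causal claim against control. The description of the ANOVA does not exclude the interaction.

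Two further objections have weight. A statistical analysis plan that is not shown may name the deciding test. And the error rates rest on a shared gain that section 3.4.4 says the control routine was designed to avoid; with no shared gain, the paired test has its nominal 5%.

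What does not fall away is what this article itself fixes: five hypotheses without a comparator, and paired tests listed as inferential on equal footing with the between-arm tests. These are statements in the text, not details lost in condensing. A design aim for the control routine is also not evidence that neither arm will change for other reasons.

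**Conclusion.** The point holds as an ambiguity with consequences. A comparison with control is intended, but the hypotheses do not say so, and section 3.5 leaves room to support them from a within-arm result.

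The size depends on how much both arms change for reasons other than the programme. For shared gains of 0.2 to 0.5 SD with 20 per arm, false support from the experimental arm alone runs from about 14% to 56% at rho 0.5, and from 27% to 92% at rho 0.8. The rule of significance in one arm only gives 12% to 25% at rho 0.5. The between-arm test of change stays at 5%, of which 2.5% is in the favourable direction. The gains and correlations are assumptions. The ranking of the rules does not depend on them once any gain is shared: only the between-arm test keeps its level whatever that gain is.

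**What to change.** - **Section 1.3:** word each of the five hypotheses as greater improvement in the experimental group than in the control group.
- **Section 3.5:** name one between-arm contrast as the only test that decides a hypothesis. The baseline-adjusted difference at week 8 is the better choice; the group-by-time contrast is acceptable. With equal SDs, the adjusted analysis has residual variance 1 − rho², against 2(1 − rho) for change scores: 0.75 against 1.00 at rho 0.5, and 0.36 against 0.40 at rho 0.8.
- **Within-arm changes:** report them as means with confidence intervals, labelled descriptive. Remove the paired and signed-rank tests as evidence of efficacy.
- **Section 4.6:** state that improvement on baseline alone does not support a hypothesis.

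The cost is wording, and within-arm p-values no longer count as evidence. No further data are needed. The plan's sample size is unchanged, since its own inputs with rho 0.5 give 34 for the group-by-time term (16 to 66 for rho from 0.8 down to 0, with f = 0.25). Whether 34 suits a between-arm d of 0.50 is a separate question: an independent t-test on post-intervention values would need 64 per group.
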